### C. Study Implementation:

1. Describe the procedures that participants will undergo. If complex, insert a table below to help the reviewer navigate.

Figure 1.

[figure not shown]

### AIM 1: Pilot & Quantitative Evaluation

AIM 1: Assess the impact of peer-mentoring approach to implementing the AIDSTAR-One Toolkit for Transition on viral suppression among ALHIV across different care facility settings (e.g. pediatric hospital, adult hospital, and primary care facilities).

### *Baseline Data Collection*

Once participants are consented and enrolled, they will complete the baseline survey and have their first blood drawn for viral load and, if necessary, resistance testing. To accommodate all literacy levels, study staff will collect survey data in face-to-face interviews with participants. Data collectors will meet with each participant in a private space in or near the health facility to go through survey questions. Surveys will be pre-tested among young adults (18 years and older) to ensure comprehension and acceptability. The baseline survey will collect socio-demographic information and assess a variety of variables that may influence the primary outcome, including internalized stigma, family dynamics, experience learning one's HIV status, alcohol use, mental health, sexual experiences, health communication self-efficacy, HIV disclosure self-efficacy, beliefs about the future, cART adherence, experiences of violence, mindfulness, and HIV treatment self-efficacy.

### *Random Assignment*

After baseline data collection, participants will be randomized to study arms. Participants randomly assigned to the usual care comparison group will receive the regular care offered at their clinic during the first intervention period. For youth who are considered clinically stable, usual care consists of three-month cART prescriptions and quarterly clinic visits. All study sites also offer monthly youth support groups, and periodically offer other activities, such as sports games and group trips, for positive youth within Ndola. Participants randomly assigned to the intervention group will begin the intervention.

### *Intervention*

AIM 1 is to assess the impact of a peer-mentoring approach to implementing the AIDSTAR-One Toolkit for Transition on viral suppression among ALHIV across different care facility settings (e.g. pediatric hospital, adult hospital, and primary care facilities). Peer mentors will be HIV-positive young adults who have successfully transitioned to self-management. These peer mentors will undergo an estimated two-week training by a Training and Capacity Building Specialist to prepare them to be skilled, valued, and paid members of the health care system. As part of their continued training, youth peer mentors will hold practice meetings with youth 18 and older. These youths will be drawn mainly from patients at the clinic whom the research team, including health care providers, know well and who are ineligible for the Project YES! study. For example, this may include participants from a previous study who are ineligible to participate in this research (see exclusion criteria) and who have stayed in contact with the research team. These practice sessions will allow the Youth Peer Mentors to further develop their skills prior to the start of the actual intervention. No data will be collected during these program practice meetings, and the information gained will inform the program only. During program activities, Youth Peer Mentors will utilize toolkit resources to facilitate discussions with youth participants about relevant issues in their lives related to their health.

At the start of the intervention, an introductory meeting will occur with the youth participant, the peer mentor, a health care provider and, if available, an interested caregiver. In the second half of this meeting, the peer mentor will meet with the youth separately to introduce him or her to the Toolkit, which includes a list of tasks adolescents should be comfortable completing as part of successful HIV self-management. We will develop a brief screening tool based on the questions included in the Toolkit (see AIDSTAR-One Toolkit attached) for the peer mentors to use to evaluate the youth's circumstances, indicate what issues may be affecting the youths' adherence, and suggest topics that may be most relevant to discuss in future meetings. The mentor will also use these tools, among others, to develop a personalized action plan with the youth. At this same time, the youth's caregiver (if

present) will meet with the healthcare provider to discuss and answer any questions the caregiver may have about the youth's HIV self-management.

After this introductory meeting, the peer mentor and youth participant will meet every month for one-on-one meetings in or near the health facility for the duration of the six-month intervention. In these one-on-one meetings, the peer mentor will use the toolkit to guide and monitor the youth's movement along the transition continuum and assess the youth's ability to self-manage his/her HIV. Each participant may interact with the toolkit materials in unique ways -- it is intended to be used as a resource, rather than a set curriculum. Peer mentors may recommend additional visits with the youth participant, as needed.

To augment this approach, youth participants will also have access to monthly youth group meetings, facilitated by peer mentors, as well as have the option to invite a caregiver to up to three caregiver group meetings over the six-month intervention period.

There will also be specific intervention components for those youth (between the ages of 15 to 24 years) preparing to move from the pediatric/adolescent clinic at ADCH to the adult HIV clinic at NTH. Once a participant is assessed by clinic staff to be ready to transition to the adult setting, they will undergo two preparatory visits at the adult clinic. First, they will visit NTH to tour the facility and meet NTH YPMs and clinic staff. Second, newly transitioned youths will also have the option to have a YPM or other familiar health staff member attend their first two visits to NTH with them to ease the transition.

Throughout the intervention, we will use several process indicators to track program implementation and participant engagement with intervention components. We will collect attendance information at every one-on-one peer mentoring session, adolescent group session, and caregiver group session. Attendance records from all sessions will be used to examine the relationship between session participation and key outcomes. Peer mentors will document the topics discussed and modules utilized at each one-on-one and group session. This information will inform final analyses and may highlight areas of particular need in this population. We will also document referrals made for additional clinical services, such as mental health services or family planning. This information will provide insight into the additional needs of our study population as well as the ability of program staff to facilitate linkage to appropriate clinical support.

#### *6-month Follow-up Data Collection*

After the completion of the first intervention period, all participants will come to the health facility to complete the 6-month follow-up survey and a second blood draw for viral load testing. The 6-month follow-up survey will assess many of the same concepts as the baseline survey in addition to questions about acceptability of the intervention (for intervention arm).

#### *Second Intervention Period (Comparison arm) & Maintenance Period (Intervention arm)*

At the end of the primary intervention period and after the 6-month follow-up data has been collected, the primary intervention group will enter a maintenance phase and the comparison group will receive the intervention. This maintenance phase will consist of individual meetings and group meetings every other month. Youth at ADCH who at this point are assessed as ready to transition physically to the adult care clinic will do so and have their maintenance phase at NTH the adult clinic.

#### *12-month Follow-up Data Collection*

After the completion of the second intervention period, all participants will come to the health facility to complete the 12-month follow-up survey and a third blood draw for viral load testing. The 12-month follow-up survey will assess many the same concepts as the baseline survey in addition to questions about acceptability of the intervention (for comparison arm).

#### *Medical Chart Review*

As part of the informed consent process, all participants will be requested to give permission for study staff to have access to their medical and pharmacy chart information at the HIV clinic, including date of HIV diagnosis, treatment regimen, WHO stages, clinical symptoms, and duration of treatment. Patient medical file data will be collected and entered into a password protected computer in an excel file. Identifying information, such as study ID and patient ID, will be used to link the data collected to merge it with the Magpi data (all this data is entered into secure servers and password protected). Trained study staff will work with the data and access to the secure server is limited to trained research staff. Once the data is merged any identifiers, e.g. patient ID number, will be destroyed to minimize risks to confidentiality.

## **AIM 2: Qualitative Evaluation**

**AIM 2:** Examine the experiences of adolescents, caregivers, health care providers, peer mentors, and study staff with the peer-mentoring/toolkit intervention.

Youth participants, who provided consent for the qualitative interview when they enrolled, will be reminded of key ethical issues prior to the in-depth interview (e.g. risks, benefits and the right to end the interview when they wish). The caregivers, peer mentors, health care providers, and study staff will also undergo an informed consent process. Trained interviewers will conduct the interviews in a private space in or near the health facility. During the interview, the participants will be asked basic socio-demographic characteristics, including sex, age, HIV status, and relationship to the ALHIV (for caregivers). Participants will also be asked open-ended questions about their experience with the intervention. Youth will additionally be asked about their personal transition to HIV self-management and/or an adult care setting as well as the role of violence victimization in this transition process.

2. Describe the number and type of study visits and/or contacts between the study team and the participant, how long they will last, and where/how they will take place.

## **AIM 1:**

Study visits will take place at or near the health facilities. Intervention arm and Comparison arm participants are required to come to the health facility 11 times (1 introduction meeting, 6 one-on-one meetings, 1 youth group meeting, & 3 data collection visits). However, youth participants in the Intervention group have the opportunity to attend up to 19 scheduled activities during the six-month intervention period and six-month maintenance period (1 introduction meeting, 6 one-on-one meetings, 6 youth group meetings + 3 data collection visits + 3 maintenance meetings). Youth participants in the Comparison group have the opportunity to attend up to 16 scheduled activities (1 introduction meeting, 6 one-on-one meetings, 6 youth group meetings + 3 data collection visits). Youth participants at ADCH who are eligible for transition to NTH will have an additional study visit to tour the facilities at NTH and meet the NTH staff (bringing their total potential visits to 20 for Intervention Arm participants and 17 for Comparison Arm participants). This tour is expected to last about 1 hour.

Peer mentoring one-on-one meetings are anticipated to last between 30 and 90 minutes. Group meetings are anticipated to last between 1 and 2 hours. The baseline data collection is anticipated to last 90 minutes, with the subsequent 6-month and 12-month follow up survey being shorter (fewer questions and randomization will have been completed). Caregivers are not required to participate in any study activities. However, caregivers have the opportunity to participate in up to four scheduled activities (1 introduction meeting & 3 caregiver group meetings).

## **AIM 2:**

One-time in-depth interviews will take place at or near one of the health clinics in a private space and will take about 1.5 hours.

## **Contacting Participants**

Study staff will contact all participants who do not attend a planned study or intervention visit. As part of routine care the clinic staff conducts home visits for YLHIV who have missed appointments to re-engage them in care. The research study will follow similar procedures if a participant misses a study visit. First, attempts will be made to contact the missing participant through the phone numbers and contacts provided during enrollment. During study enrollment, the research team will confirm the appropriate phone numbers and phone ownership (in an earlier study among this population, 69% of 309 youth use cell phones). The team will also request permission to contact the youth's caregiver, or the caregiver's contact, to inquire about the missing participant as well. If the missing participant cannot be reached the trained study interviewers will go to the home to inquire. At the home, the study staff will inquire about the youth using a script, but will not discuss the research study or disclose the youth's participation. If no one is home or they are asked to follow-up later, they will attempt to reach the participant three times before considering the participant lost to follow-up. This process has received approval from the Zambia and Hopkins IRBs for previous studies and has worked well. Participants lost to follow-up will not be replaced in the study.

3. Describe the expected duration of the study from the perspective of the individual participant and duration overall.

The official study period is from May 15, 2016 to June 30, 2019. From a participant's perspective, the overall duration will be about 18 months – 2 months for recruitment and baseline data collection, 6 months for the initial intervention, 2 months for midline data collection, 6 months for the comparison group to receive the intervention and the initial intervention group to receive maintenance care and 2 months for endline data collection. However, recruitment and follow-up interviews between sessions may take less time.

4. Provide a brief data analysis plan and a description of variables to be derived.

### **Aim 1 & Sub-Aim 1A Quantitative Analyses**

The primary analysis to assess impact will use generalized estimating equation (GEE) (22) to compare the intervention to the comparison arm on VL suppression. This process will also be used to examine other key outcomes over time, such as self-reported medication adherence and internalized stigma.

This approach accounts for within subject correlations due to repeated measures. We will use GEE models with appropriate link functions (e.g., identity for continuous data, logit for binary data) and variance functions (e.g., identity for continuous data, logit for binary data) and variance functions (e.g., normal for continuous data, binomial for binary data). Unstructured working correlation matrices will be used in all models. The primary outcome will be cART adherence as measured by viral load suppression  $\leq 1,000$  copies/mL. In the stratified analysis (aims 1A), the models described above will be fit separately to two sub-samples of study participants – those participants who started the intervention in a pediatric care setting (i.e. ADCH) and those participants who started the intervention in an adult care setting (i.e. NTH, Twapia Clinic, and Lubuto Clinic). We will also examine pre- and post-intervention effects, and if outcomes change over time, at the 6-month and 12-month follow-ups. Secondary outcomes will include adolescents' transition status, including how many adolescents physically transitioned to adult care from the children's hospital.

Descriptive statistical methods will be used to assess the feasibility and acceptability of the intervention. The study team will also analyze attendance and the reasons for missed sessions. Together these data will provide valuable information on the feasibility of the intervention and participant exposure to intervention elements.

Finally, secondary data analyses will be carried out on participants' reported experiences of violence victimization. Descriptive statistics will be used to obtain weighted estimates of the youth's

lifetime and past-year prevalence of physical, psychological, and sexual violence victimization, with percentages and 95% confidence intervals. Logistic regression will be conducted to examine associations between youth's violence victimization and VL suppression, with GEE models to account for the potential correlations between youth's responses from the same clinic. Associations between violence victimization and VL suppression will further be assessed using propensity scores. Such analyses will shed light on the prevalence of violence victimization and its relationship with VL within a population of youth living with HIV in Zambia, which will inform the potential integration of violence-focused content into the intervention.

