## JHSPH IRB Research Plan for New Data Collection

**PI Name:** [name]  
**Study Title:** Transitioning Adolescents to HIV Self-Management in Zambia  
 (Known as: Project YES: Youth Engaging for Success)  
**IRB No.:** IRB00007870  
**PI Version No. / Date:** 5 / September 7, 2018

**I. Aims of the Study:** Describe the aims/objectives of the research and/or the project's research questions or hypotheses.

The specific objectives of the study are to:

AIM 1) Assess the impact of a peer mentoring approach to implementing the AIDSTAR-One toolkit on viral suppression and other HIV-related outcomes such as retention in care and adherence to cART, among transitioning youth in different care facility settings (e.g., pediatric hospital, adult hospital, and primary care facilities). Hypothesis: Youth in the intervention arm will experience greater HIV viral suppression at the end of six months of the intervention than youth in the comparison arm.

AIM 1a) Conduct a stratified analysis to examine the impact of a peer mentoring approach separately among: a) the 144 youth participants (15-24) transitioning out of an adolescent clinic into an adult clinic; and b) among 144 youth participants (15-24) who are already attending adult care. This will be a sub-analysis of the larger study to determine the effects of the intervention among these two distinct groups of adolescents and youth.

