### III. Study Design:

- A. Provide an overview of your study design and methods. The study design must relate to your stated aims/objectives. Details will be requested later. If your study also involves analysis of existing data, please complete Section XI, “Secondary Data Analysis of Existing Data” in the last part of this research plan. If your study ONLY involves analysis of existing data, please use the research plan template for secondary data analysis (JHSPH IRB Research Plan for Secondary Data Analysis of Existing Data/Specimens).

The study is a randomized controlled trial at the individual level that uses a stepped wedge design to assess the peer-mentoring/AIDSTAR-One toolkit intervention. The study team will test a six-month peer-mentoring program among 144 YLHIV in an intervention arm compared to 144 YLHIV in a comparison arm. Participants for the RCT will be consecutively selected from two hospitals -- Arthur Davison Children’s Hospital (ADCH) and Ndola Teaching Hospital (NTH) – and two primary care clinics (PCCs) – Twapia Clinic and Lubuto Clinic. The participating facilities were purposively selected because they represent different models of care. ADCH is a hospital for children and serves older youth who should ultimately transition to adult care. In contrast, NTH and the two primary care clinics are essentially adult HIV care settings. While they were not designed to initially serve HIV positive adolescents, they continue to experience a growth in the number of enrolled adolescents. The PCCs were purposively selected based on their high ALHIV patient populations, designated ART center status, and proximity to other study sites.

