After the completion of the initial 6-month intervention and the subsequent 6-month follow-up assessment among participants in both arms, the primary intervention group will enter a maintenance phase and the comparison group will receive the intervention for six months. Assessments, including a survey and a blood draw for VL testing, will occur at baseline, at the end of the first six months, and at the end of 12 months (see Figure 1 under study implementation). Resistance testing will also be conducted at baseline for those participants who have a VL failure, defined as 1000 copies/ml or higher. Resistance testing is critical for this study as the primary outcome is viral suppression, something that will not occur if a participant has a resistant strain and is not on the correct treatment, no matter how adherent s/he may be. Routine VL results from among ADCH patients reveals that approximately 50% of adolescents have VL failure. Based on that data, we estimated that 50% of the 288 participants in this research (n=144) will have VL failure and need resistance testing.

At the end of the initial 6-month intervention, we will begin conducting qualitative in-depth interviews with participants, their caregivers when possible, and the health care providers, peer mentors, and study staff involved in delivering the program. These data will provide contextual details and experiences to help interpret the study findings and determine what aspects of the intervention were valued.

- B. Provide a sample size and a justification as to how you arrived at that number. If you use screening procedures to arrive at a final sample a table may be helpful.

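### The primary GEE is not tied to the 6-month contrast that the protocol hypothesises and powers, and its wording admits tests with a smaller effect or less power

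*Protocol*

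**What the plan says.** **Hypothesis.** Section I (Aims of the Study) expects in the intervention arm "greater HIV viral suppression at the end of six months of the intervention than youth in the comparison arm".

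**Power.** Section III.B (AIM 1 Calculations) takes 144 per arm, 20% loss to follow-up and a 5% type 1 error. It claims over 85% power for 50% against 70% suppressed at the six-month data collection.

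**Design.** Section III.A calls the trial a "randomized controlled trial at the individual level that uses a stepped wedge design". Viral load is measured at baseline, 6 months and 12 months. After the 6-month assessment, "the primary intervention group will enter a maintenance phase and the comparison group will receive the intervention for six months". Section V.C.1 (12-month Follow-up Data Collection) places the third blood draw after that second intervention period.

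**Analysis.** Section V.C.4 (Aim 1 & Sub-Aim 1A Quantitative Analyses) states: "The primary analysis to assess impact will use generalized estimating equation (GEE) (22) to compare the intervention to the comparison arm on VL suppression". It says the method handles within-subject correlation from repeated measures, gives link and variance functions, and sets an unstructured working correlation for all models. The visit-specific looks come later: "We will also examine pre- and post-intervention effects, and if outcomes change over time, at the 6-month and 12-month follow-ups". The same models are refitted in the two Sub-Aim 1A strata.

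**The concern.** Only the 6-month visit compares youth who have been offered the intervention with youth who have not. At baseline no effect can exist. At month 12 both arms have been offered it. The section that defines the primary test does not say which visit or coefficient carries that test, and its order of sentences presents the timed contrasts as extras. The stepped-wedge label also suggests an analysis that uses every period.

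At least three models fit the words: one arm effect across visits, an arm-by-time change from baseline to month 6, and a 6-month contrast adjusted for baseline. They do not estimate the same quantity and differ widely in power. Leaving the choice open risks a primary test weaker than the one powered, or a choice among them made after the data are seen.

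**Working it through.** **Inputs from the protocol.** 144 per arm; 20% loss, so 144 × 0.8 = 115.2, taken as 115; 50% against 70% at month 6; 5% error, taken as two-sided because sidedness is not stated.

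**Assumptions, not in the protocol.** Baseline suppression is 50% in both arms. The intervention arm holds 70% at month 12. The comparison arm reaches 70% (full catch-up) or 60% (half catch-up) at month 12. Visits have equal weight. Within-person correlation ρ is 0.3, 0.5 or 0.7. Calculations are on the proportion scale as an approximation to the logit model.

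**1. The stated power.** Two-proportion test with pooled null variance:

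- Null SE = √(2 × 0.6 × 0.4 / 115) = 0.0646; alternative SE = √((0.21 + 0.25) / 115) = 0.0632.
- Power = Φ[(0.20 − 1.96 × 0.0646) / 0.0632] = Φ(1.16) = 87.7%. With unpooled variance it is 88.5%.

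This agrees with over 85%. The powered quantity is therefore a plain 6-month comparison of two proportions.

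**2. One arm effect across visits.** The effect is the mean of the visit differences. Each arm's variance is the sum over visit pairs of s_j s_k ρ_jk, divided by the squared number of visits and by 115, with s = √(p(1 − p)). Power = Φ(effect/SE − 1.96).

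Example: months 6 and 12, full catch-up, ρ = 0.3.

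- Effect = (0.20 + 0)/2 = 0.10.
- Intervention arm: (0.21 + 0.21 + 2 × 0.3 × 0.21)/4 = 0.1365.
- Comparison arm: (0.25 + 0.21 + 2 × 0.3 × 0.2291)/4 = 0.1494.
- SE = √(0.2859/115) = 0.0499; power = Φ(0.046) = 52%.

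| Visits pooled | Catch-up | Effect (points) | ρ = 0.3 | ρ = 0.5 | ρ = 0.7 |
|---|---|---|---|---|---|
| 6, 12 | full | 10 | 52% | 46% | 42% |
| 0, 6, 12 | full | 6.7 | 30% | 25% | 22% |
| 6, 12 | half | 15 | 84% | 79% | 73% |
| 0, 6, 12 | half | 10 | 57% | 48% | 42% |

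**3. Change from baseline to month 6 (arm-by-time term).** The effect stays at 20 points. The summed variance is (0.25 + 0.21 − 2ρ√(0.25 × 0.21)) + (0.50 − 0.50ρ) = 0.96 − 0.958ρ.

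- ρ = 0.3: SE = √(0.6725/115) = 0.0765, power 74%.
- ρ = 0.5: SE = √(0.4809/115) = 0.0647, power 87%.
- ρ = 0.7: SE = √(0.2892/115) = 0.0501, power 98%.

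For 85% power the SE must be at most 0.20/(1.96 + 1.036) = 0.0667. That requires 0.96 − 0.958ρ ≤ 0.512, so ρ of about 0.47 or more.

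**4. Six-month contrast adjusted for baseline.** The variance is multiplied by about (1 − ρ²).

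- ρ = 0.3: SE = √(0.46 × 0.91/115) = 0.0603, power 91%.
- ρ = 0.5: SE = √(0.46 × 0.75/115) = 0.0548, power 95%.
- ρ = 0.7: SE = √(0.46 × 0.51/115) = 0.0452, power 99%.

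At each of these correlations this model has the most power, and it uses data already collected.

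**The case against.** The strongest reply is that no sentence puts month 12 into the primary test. Baseline and month 6 alone are repeated measures, and a three-visit GEE with visit-specific arm terms can test the 6-month difference exactly. The aims and the sample size section both name six months, and the comparison arm is deliberately held untreated until then, so month 6 is the natural reading. The section answers a form that asks for a brief analysis plan, and a statistical analysis plan that was not available may supply the contrast. The low pooled power figures rest on an unstated model and an assumed catch-up.

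Much of this stands. A reader might infer that the primary test averages in month 12 and so is not the 6-month effect. The documents do not support that: month 12 appears only in the sentence on additional looks. An unstructured working correlation matters only with three or more visits, which hints at a three-visit model, but that choice covers all models and settles nothing about the primary contrast. The pooled figures show what one permitted reading would cost.

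Two things remain. The section goes beyond a bare outline: it fixes the method, links, variance functions and working correlation, yet leaves out what decides the tested quantity and lists the month-6 look as an extra. And the more favourable change-from-baseline reading still falls short of the stated power when ρ is below about 0.47.

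**Conclusion.** The concern holds as a failure to tie the primary analysis to the hypothesised and powered contrast. The power calculation itself is sound: 87.7% reproduces the stated over 85% for a 6-month two-proportion comparison.

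The cost depends on which model is run. A single arm effect that includes month 12 would shrink to about 7 to 10 points with about 22% to 52% power under full catch-up. With half catch-up, pooling months 6 and 12 gives 84% to 73%. A change-from-baseline test at month 6 gives 74% at ρ = 0.3 and 87% at ρ = 0.5. A baseline-adjusted 6-month contrast gives 91% and 95%. Catch-up, visit weights and correlation are all assumed, because the protocol gives none of them.

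It cannot be concluded that the trial will run a diluted test, only that the text allows one. The ambiguity also carries into Sub-Aim 1A, where the same models are used in each stratum.

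**What to change.** In section V.C.4:

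- State that the primary test is the between-arm difference in viral suppression at the 6-month visit.
- Take it from a model with visit-specific arm effects, with baseline suppression status adjusted for or constrained equal across arms. Name the visits in the model and the coefficient tested.
- List all 12-month and pre/post contrasts as secondary, noting that the comparison arm has been offered the intervention by month 12.
- Apply the same definition in the Sub-Aim 1A strata.

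In section III.A, describe the design as an individually randomised parallel-arm trial with delayed intervention in the comparison arm, in place of stepped wedge.

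The cost is wording and a minor change to the analysis code. No extra participants, visits or blood draws are needed.
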